### Interim analyses {21b}

Interim analysis will be performed when approximately 10% of our sample have completed follow-up assessments. The preliminary findings will be presented in conference to promote our study.

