### Sample size {14}

#### Cognitive function

The sample size (alpha 0.05, power 0.80) required to detect significant differences in global cognitive function over 6 months as assessed by ADAS-Cog between intervention and control groups is estimated using G*Power 3.1. Based on a similar RCT of 8-week calligraphy training in local older people with MCI living in care homes [26], the effect size (ES) on cognitive outcome was estimated to be 0.56. However, because the participants of this study are younger, less frail, living actively in the community, and at an earlier stage of AD, a relatively larger cognitive response (ES=0.70) is anticipated as suggested by a previous review of complex mental activity on cognition [46]. Nevertheless, because the control group will have ongoing calligraphy practice, the additional cognitive benefits arising from doubling the participation in calligraphy in the intervention group is anticipated to be lowered by a conservative estimate of 50%. Taking into consideration the effect of covariates on the cognitive outcome and an estimated drop-out rate of 20%, a total of 112 participants will be required for this study.

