## Assignment of interventions: Blinding

### Who will be blinded {17a}

Participants are assumed to be not blinded to the intervention. Nevertheless, they will be instructed not to discuss their allocation with other participants or outcome assessors. To reduce the possible expectancy bias, participants will be explained at the time of giving consent that there is no evidence to support a difference in cognitive benefit between the two arms. The research assistant who assists in consent seeking and monitoring of progress and adverse events will not be involved in outcome assessment. The assessor who will be another trained research assistant will be blinded to the randomization status and will not be involved in the intervention. The statistician responsible for the randomization is not involved in other parts of the study including data analysis.

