## Oversight and monitoring

### Composition of the coordinating centre and trial steering committee {5d}

Weekly meetings will be held among the principal investigator and the research staff to monitor the project progress, identify and address any problems in subject recruitment, intervention delivery, and data collection, field work logistics, budget and response to major enquiries, and possible adverse events.

Monthly meetings will be held together with the co-investigators and the director of our collaborating centres to discuss the project progress, address any issues with the study logistics, review the results, and prepare for reports and publications.

To ensure good governance, quarterly meetings will be held together with the Department Chair to review project progress, outcomes, and important decisions to be made in relation to the funding and logistics, such that the project is implemented according to plan with the proposed goals achieved.

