### Composition of the data monitoring committee, its role and reporting structure {21a}

The principal investigator and co-investigators will monitor the data collection and storage to ensure that the data is kept and used in accordance to the protocol. Data monitoring committee is not considered as practising calligraphy is a low-risk intervention, and our study is not supported by any sponsor.

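### An interim look at about 11 of 112 participants, with conference promotion as its only stated use, puts the remaining outcomes at avoidable risk and informs no decision

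*Protocol article*

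**What the plan says.** Interim analyses {21b} has two sentences. The first sets the trigger: "Interim analysis will be performed when approximately 10% of our sample have completed follow-up assessments". The second gives the use: "The preliminary findings will be presented in conference to promote our study". It names no decision, boundary or restriction on access.

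Four other sections bear on this:

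- **Data monitoring committee {21a}:** "Data monitoring committee is not considered as practising calligraphy is a low-risk intervention".
- **Who will be blinded {17a}:** participants are taken to be unblinded. Against expectancy bias, they are told at consent that "there is no evidence to support a difference in cognitive benefit between the two arms". The same section blinds the outcome assessor and tells participants not to discuss their allocation.
- **Coordinating centre and trial steering committee {5d}:** monthly meetings of the investigators with the directors of the collaborating centres are to "review the results, and prepare for reports and publications".
- **Sample size {14}, Cognitive function:** "a total of 112 participants will be required for this study".

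**The concern.** An early look at outcomes by arm is normally justified by a decision it serves and by limits on who sees it. Here the stated use is publicity, and no limit on access is given.

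The design is sensitive to early disclosure for three reasons:

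- Participants know their arm, so what they believe about the benefit of doubling practice can affect effort at testing, adherence and willingness to return.
- The contrast depends on controls keeping to their usual amount of calligraphy, an activity they can increase at will.
- The message meant to restrain expectancy is that nothing favours either arm. A presented early result pulls against it in whichever direction it happens to fall.

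Distortion of this kind is hard to repair in the analysis, because it alters what participants do rather than how the data are handled.

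**Working it through.** **Inputs from the article.** N = 112; 1:1 allocation; 20% drop-out; effect size 0.70 ("a relatively larger cognitive response (ES=0.70) is anticipated") halved for the active control, so 0.35; recruitment from 15 January 2020 to 31 December 2021, about 23.5 months; follow-up 6 months.

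**Size of the look.** 0.10 × 112 = 11.2, so about 11 people, or 6 versus 5. With 20% drop-out, 112 × 0.8 = 89.6 outcomes are expected. Then 11.2/89.6 = 12.5% are in hand and 87.5% outstanding. Counted against all 112, 90% are outstanding.

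**Precision, unadjusted.**

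- SE = √(1/6 + 1/5) = 0.606 SD.
- Half-width of the 95% interval = t(9; 0.975) × SE = 2.262 × 0.606 = 1.37 SD.
- If the true effect is 0.35 SD, P(wrong sign) = Φ(−0.35/0.606) = 0.28.
- P(|estimate| > 0.5 SD) = 0.40 + 0.08 = 0.48.
- Power at the look is about 8%.

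**Precision with covariate adjustment.** The plan adjusts for covariates but does not state how strongly they predict the outcome. Let r be the assumed outcome–covariate correlation and multiply the SE by √(1 − r²).

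The value r = 0.81 is a favourable case because it is about what the sample size would need. The plain two-sided calculation at 0.35 gives 129 per arm, 258 in total. With r = 0.81 the total falls to 90, and 90/0.8 = 112.5, rounded up to 113. So 112 is approached only with an input the article does not state. That is a separate matter and does not affect this point.

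| r (assumed) | SE (SD) | Half-width (SD) | Wrong sign | Absolute size > 0.5 SD |
|---|---|---|---|---|
| 0 | 0.606 | 1.37 | 28% | 48% |
| 0.5 | 0.606 × 0.866 = 0.524 | 1.2 | 25% | 44% |
| 0.81 | 0.606 × 0.586 = 0.355 | 0.8 | 16% | 34% |

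The adjusted rows keep 9 degrees of freedom, which is generous. Even in the best row the half-width is more than twice the planned effect (0.8/0.35 = 2.3). In the unadjusted row it is about four times (1.37/0.35 = 3.9).

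**Timing.** Assume uniform accrual.

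- Without drop-out, the trigger falls at 0.10 × 23.5 + 6 = 8.35 months, when 8.35/23.5 = 36% are recruited (about 40 of 112).
- With 20% drop-out, it falls at 0.125 × 23.5 + 6 = 8.94 months, when 38% are recruited (about 43 of 112).

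Recruitment would already be closed at the trigger only if those first 11 or so completers had been enrolled no earlier than the last 6 months, that is after month 23.5 − 6 = 17.5. The conference date is not given and could be later than the trigger.

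**Type I error.** If the look were tested at 0.05 and could lead to a claim, the overall error would be about 0.094 to 0.095. No such claim is planned, so this does not apply.

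**The case against.** The strongest reply is that the harm needs a chain of events that the article does not state. The text says preliminary findings, not results by arm. It gives no conference date, and recruitment might have been slow at first, as the Discussion expects. It describes no route from a conference to older participants in Hong Kong. An unseen full protocol or analysis plan may control access. The outcome assessor is blinded, and practice time is logged in both arms, so extra practice by controls would be visible.

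Much of this stands, and it rules out several stronger readings that a reader might infer:

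- **That the consent statement becomes untrue.** An estimate this imprecise is not evidence of a difference. The risk is to what participants believe.
- **That the statement is the only protection.** Assessor blinding and the instruction not to discuss allocation are separate safeguards. The statement is the only measure aimed at participant expectancy.
- **That centre directors will see early results by arm.** Section {5d} says results are reviewed, but not by arm and not before database lock.
- **That assessors would be unblinded.** An aggregate result reveals no individual's allocation.
- **That the final test is inflated.** No early stopping or efficacy claim is planned.

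The objection does not remove the core. The section itself fixes the look, its trigger and its promotional use, and this is not detail that an article leaves out. Logging practice would show contamination but not prevent it. If only pooled or baseline data are meant, the section should say so.

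**Conclusion.** The point holds as an avoidable risk to trial conduct. As written, the plan analyses data from about 11 of 112 people and presents them while about 90% of outcomes are uncollected (87.5% of those expected after drop-out), for no stated decision and without independent monitoring.

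The estimate would have a half-width of 0.8 to 1.37 SD against a planned 0.35 SD, and would point the wrong way 16% to 28% of the time. The range depends on an assumed covariate correlation between 0 and 0.81. These figures measure how little the look would tell anyone. The size of any effect on expectancy, control-arm practice, adherence or retention cannot be derived from the article.

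Two inferences carry the conclusion: that findings triggered by completed follow-up are outcomes by arm, which is the natural reading, and, for the effect on new recruits only, that recruitment was still open, which holds under uniform accrual. Participants already enrolled and awaiting follow-up are exposed if the presentation comes soon after the trigger, whatever the state of recruitment.

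**What to change.** - In Interim analyses {21b}, remove the by-arm interim outcome analysis and its presentation.
- Limit any conference report before the last follow-up (T1) visit to baseline data and to recruitment, adherence and data-quality information pooled over arms.
- In section {5d}, state that meetings before database lock do not see outcomes by arm.
- Because Trial status reports that recruitment has ended, the final report should say whether and when the look and the presentation took place, and who saw the results.

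The cost is the loss of an early promotional abstract. Sample size, assessments and the final analysis are unchanged.

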### Methods for additional analyses (e.g. subgroup analyses) {20b}

Sensitivity analysis will be performed for participants who complete the intervention and all assessments, and a secondary analysis will be conducted to identify any differences in the effect of intervention among participants with different amounts of calligraphy practice at baseline.

### Methods in analysis to handle protocol non-adherence and any statistical methods to handle missing data {20c}

In our electronic data entry, the record cannot be submitted unless all the data have been entered, thus minimizing missing data. Adherence to intervention, which is recorded by our trained research assistants on a weekly basis, serves as a covariate and will be included in the data analysis.

### Plans to give access to the full protocol, participant-level data and statistical code {31c}

The full protocol has already been submitted to the Clinical Trials Registry (ChiCTR). The data of this study will be available from the principal investigator upon reasonable request.

## Oversight and monitoring

### Composition of the coordinating centre and trial steering committee {5d}

Weekly meetings will be held among the principal investigator and the research staff to monitor the project progress, identify and address any problems in subject recruitment, intervention delivery, and data collection, field work logistics, budget and response to major enquiries, and possible adverse events.

Monthly meetings will be held together with the co-investigators and the director of our collaborating centres to discuss the project progress, address any issues with the study logistics, review the results, and prepare for reports and publications.

To ensure good governance, quarterly meetings will be held together with the Department Chair to review project progress, outcomes, and important decisions to be made in relation to the funding and logistics, such that the project is implemented according to plan with the proposed goals achieved.

### Composition of the data monitoring committee, its role and reporting structure {21a}

The principal investigator and co-investigators will monitor the data collection and storage to ensure that the data is kept and used in accordance to the protocol. Data monitoring committee is not considered as practising calligraphy is a low-risk intervention, and our study is not supported by any sponsor.

### Adverse event reporting and harms {22}

Adverse events are expected to be minimal in this study, as no drug treatment or invasive procedure is involved, and the intervention (calligraphy) is already familiarized to the participants. Nevertheless, mild discomforts such as fatigue or muscle soreness due to prolonged sitting and writing and headache or eye soreness due to intense concentration in calligraphy practice may be experienced by some participants. These potential discomforts will be explained to participants before signing consent. Participants will be advised to report to our research assistant any health problems or suspected adverse events during the study period. All complaints with regard to our intervention will be documented, and any adverse events potentially due to our intervention will be assessed and followed by the principal investigator. The intervention will be stopped immediately if the reported event is considered to be related.

### Frequency and plans for auditing trial conduct {23}

As per the university’s requirement, an independent auditor will conduct an annual review throughout the project period.

### Plans for communicating important protocol amendments to relevant parties (e.g. trial participants, ethical committees) {25}

There is no plan for modifying the protocol at this juncture. Any proposed changes to the protocol will be subjected to review and approval by the ethics committee before adoption. Any deviations from the Protocol will be fully documented using a breach report form.

### Dissemination plans {31a}

Study findings will be published in peer-reviewed journals and disseminated to community centres. The funder has no role or restriction in the decision of publication.

## Discussion

Our anticipated findings will provide scientific evidence to the underlying mechanisms of how intellectual activities improves cognitive function. With the newer generations of older people being much better educated, being more health conscious, and having a more active and intellectually enriched lifestyle in their life course [48], their cognitive reserve is likely to be higher, and their risks of dementia are likely to be different from the previous and existing cohorts [49]. Testing whether increasing participation in habitual intellectual activities can further enhance the FC of DMN and thereby reinforce resilience to cognitive decline would be more tailored to the risk profile of this upcoming older population and can provide people with high cognitive reserve some evidence that stepping up their usual practice of intellectual activities is a useful strategy in promoting cognitive maintenance.

Due to social unrest in late 2019 and the COVID-19 pandemic since January 2020, the recruitment rate is expected to be slower than planned. Intervention is unlikely to be affected because calligraphy practice is home-based.

## Trial status

The study was initially planned to commence in September 2019 and complete in 2 years. Due to social unrest in late 2019 and the COVID-19 pandemic since January 2020, an extension of the study period has been granted, with the revised completion date on 31 December 2022.

The protocol version 1 was dated 30 December 2018, and version 2 was dated 29 February 2019. Reasons for revision are described in {3}.

Subject recruitment began on 15 January 2020 and ended on 31 December 2021.

## Abbreviations

AAL: Automated anatomical labelling
AD: Alzheimer’s disease
ADAS-Cog: Alzheimer’s Disease Assessment Scale-Cognitive Subscale
AMIC: Abbreviated Memory Inventory for Chinese
ChiCTR: Chinese Clinical Trial Registry
CVFT: Chinese verbal fluency test
DMN: Default mode network
DSB: Digit span backward
DSF: Digit span forward
ES: Effect size
FC: Functional connectivity
FOV: Field of view
HF+: Parahippocampal cortex
HK-MoCA: Hong Kong Chinese version of Montreal Cognitive Assessment
IPL: Inferior parietal lobe
LTC: Lateral temporal cortex
MCI: Mild cognitive impairment
MIC: Memory Inventory for Chinese
MNI: Montreal Neurological Institute
mPFC: Medial prefrontal cortex
PCC: Precuneus/posterior cingulate cortex
RCT: Randomized controlled trial
ROIs: Regions of interest
rs-fMRI: Resting-state functional magnetic resonance imaging
SCD: Subjective cognitive decline
sMRI: Structural MRI
SPM12: Statistical Parametric Mapping software
TE: Echo time
TMT-A: Trail making test
TR: Repetition time
WHO-ICTRP: International Clinical Trial Registration Platform of World Health Organization
